## Abstract

**Background:**

Androgen deprivation therapy (ADT) is accompanied by a number of adverse side effects including reduced bone mass and increased risk for fracture, reduced lean mass and muscle strength, mood disturbance and increased fat mass compromising physical functioning, independence, and quality of life. The purpose of this investigation is to examine the effects of long term exercise on reversing musculoskeletal-related side effects, and cardiovascular and diabetes risk factors in men receiving androgen deprivation for their prostate cancer. Specifically, we aim to investigate the effects of a 12-month exercise program designed to load the musculoskeletal system and reduce cardiovascular and diabetes disease progression on the following primary endpoints: 1) bone mineral density; 2) cardiorespiratory function and maximal oxygen capacity; 3) body composition (lean mass and fat mass); 4) blood pressure and cardiovascular function; 5) lipids and glycemic control; and 6) quality of life and psychological distress.

**Methods/Design:**

Multi-site randomized controlled trial of 195 men (65 subjects per arm) undergoing treatment for prostate cancer involving ADT in the cities of Perth and Brisbane in Australia. Participants will be randomized to (1) resistance/impact loading exercise, (2) resistance/cardiovascular exercise groups and (3) usual care/delayed exercise. Participants will then undergo progressive training for 12 months. Measurements for primary and secondary endpoints will take place at baseline, 6 and 12 months (end of the intervention).

**Discussion:**

The principal outcome of this project will be the determination of the strength of effect of exercise on the well established musculoskeletal, cardiovascular and insulin metabolism side effects of androgen deprivation in prostate cancer patients. As this project is much longer term than previous investigations in the area of exercise and cancer, we will gain knowledge as to the continuing effects of exercise in this patient population specifically targeting bone density, cardiovascular function, lean and fat mass, physical function and falls risk as primary study endpoints. In terms of advancement of prostate cancer care, we expect dissemination of the knowledge gained from this project to reduce fracture risk, improve physical and functional ability, quality of life and ultimately survival rate in this population.

**Clinical Trial Registry:**

A Phase III clinical trial of exercise modalities on treatment side-effects in men receiving therapy for prostate cancer; ACTRN12609000200280

## Background

Worldwide prostate cancer is the second most common cancer in men representing 19% of cancers among men in developed countries [1]. With the aging of the population in developed and developing countries the incidence of all cancers, which are normally higher in those aged > 65 years, is predicted to substantially rise, particularly for colon and prostate cancer which are well established aging-related cancers [2]. Advancing age not only increases the vulnerability to cancer but also the risk for other comorbid conditions (e.g. osteoporosis, arthritis and sarcopenia, cardiovascular disease) [3] that can compromise physical function and independent living with substantial costs to the community ultimately culminating in death. The introduction of the prostate specific antigen (PSA) blood test into routine clinical practice in Australia and the USA in the 1990s has led to earlier diagnosis of disease [4,5]. Men are often minimally symptomatic or, more often, completely asymptomatic and can be expected to survive substantially longer than their historical counterparts [5,6]. Full characterization of toxicity of androgen deprivation therapy (ADT) is now seen to be an important priority for research [6-8].

The use of ADT to reduce testosterone levels in men with prostate carcinoma is accompanied by a number of adverse side effects that include reduced bone mass and increased risk for fracture at multiple sites [9,10], reduced lean mass and muscle strength [11,12], and increased fat mass [11] compromising physical functioning, independence, and quality of life [13]. Existing treatments to alleviate these side effects have been predominantly pharmacological; however, they are expensive and are not accompanied by improved physical function. Of equal concern are recent indications of increased incidence of coronary and metabolic complications associated with ADT which raises major problems of therapy toxicity that are beyond those related to the musculoskeletal system [14]. As well, ADT is associated with increased emotional distress [15] and men with advanced prostate cancer experience higher levels of psychological distress and poorer quality of life by comparison to men with localized disease [16,17]. Finally, as there is unquestionable evidence of the effectiveness of regular exercise in prevention and management of several chronic diseases including cardiovascular disease and diabetes, and even premature death [18,19], prostate cancer patients on ADT may particularly benefit from exercise by reducing the risk of co-morbidity associated with therapy. Preliminary clinical trials by our team [20-23] and others [24,25] suggest high efficacy of exercise for these patients. However, the optimal mode of exercise is yet to be established, the gamut of side-effects of ADT has not been addressed in a single study, and long term interventions, which are more clinically relevant and necessary to assess bone outcomes, have never been attempted. Of critical importance is patient retention and compliance with long term exercise prescription. We have successfully completed several phase 1 and 2 clinical trials and this paper describes our current phase III trial, where our aims are to examine the longer terms effects of exercise modality, dosage and patient population implementation. The penultimate outcome will be clinical guidelines for the prescription of exercise for the management of ADT treatment side effects in all men receiving such therapy for their prostate cancer resulting in greatly improved survival, quality of life, function and structure.

The purpose of this investigation is to examine the effects of long term exercise on reversing musculoskeletal-related side effects, and cardiovascular and diabetes risk factors in men receiving ADT for their prostate cancer. Specifically, we aim to investigate the effects of a 12-month exercise program designed to load the musculoskeletal system and reduce cardiovascular and diabetes disease progression on the following primary endpoints: 1) bone mineral density (BMD); 2) cardiorespiratory function and maximal oxygen capacity; 3) body composition (lean mass and fat mass); 4) blood pressure and cardiovascular function; and 5) lipids and glycemic control. Secondary endpoints will include: 1) physical and neuromuscular function; 2) balance and risk of falls; and 3) quality of life and psychological distress.

This project is unique as it utilizes impact-loading exercise in addition to resistance exercise as a means to counteract adverse musculoskeletal treatment related side effects (e.g. osteoporosis and sarcopenia) of ADT treated patients with prostate cancer. Further, this study also examines the effects of cardiorespiratory (aerobic) and resistance (anabolic) exercise as a means to counteract adverse body composition, cardiovascular and glucose metabolism co-morbidities related to treatment by ADT for patients with prostate cancer. Importantly, by comparing clinic versus home based exercise in one of the groups we will learn much about efficacy and feasibility of the home setting for more practical whole of patient population treatment. Finally, the extent to which anabolic versus aerobic exercise may ameliorate psychological distress and enhance quality of life will be assessed. This is the first study to our knowledge which is specifically designed to address all of these major side effects of ADT in a long term clinical trial.

## Methods/Design

### Overview

Subjects will be recruited by invitation of their attending specialist and from the Prostate Cancer Foundation of Australia interest groups. Those entering the study will undertake a series of familiarisation sessions and baseline measurements prior to randomization to (1) 12 month program of resistance/impact loading exercise, (2) 12 month program of resistance/cardiovascular exercise and (3) 6 months usual care (no planned exercise) followed by 6 months of exercise (delayed). In addition to the twice weekly training in the clinic setting, all groups will also undertake twice weekly exercise sessions at home as specified below. During the course of the study, subjects will be encouraged to maintain customary activity and dietary patterns (Figure 1). This protocol has been approved (ID: 08-69 [name]) by the University Human Research Ethics Committee.

**Figure 1 F1:**
[figure not shown]
**CONSORT Diagram**.

### Subjects

195 men (65 subjects per arm) undergoing treatment for prostate cancer involving ADT with no regular exercise (undertaking structured aerobic or resistance training two or more times per week) within the past 3 months will be recruited by invitation of their attending specialist in the Perth and Brisbane areas. All participants will have been hypogonadal for a period of at least 2 months prior to commencing the program, and to anticipate remaining so for the duration of the study. Subjects will be stratified according to time on ADT (< or = 6 months) and randomly assigned to one of the groups listed above. Individuals with established metastatic bone disease, established osteoporosis and those taking medications known to affect bone metabolism, such as bisphosphonates, will be excluded from participation.

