### Measurements

Measurements for primary and secondary endpoints will take place at baseline, 6 and 12 months (end of the intervention).

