### Calculation of Sample Size and Statistical Analysis

Data from our 20-week [20] and 36-week [28] preliminary studies in prostate cancer patients indicate that the standard deviation (SD) for change in our primary outcome of BMD equates to ~4.8%, 3.3%, and 2.5% for the hip, lumbar spine, and total body, respectively. With ADT, the annual loss is reported to be 2–8% at the spine and 1.8–6.5% at the hip [35], and based on our 36-week data, we obtain an annualized loss for the total body of 3.5%. However, loss in BMD is greatest in the first year of ADT [36], although continued losses are reported beyond this time period [36,37]. Consequently, as participants will have been on ADT for varying time periods and based on studies to date, we anticipate losses of ~3% and 2.5% at the clinically relevant fracture sites of the spine and hip, and 1.5% for the whole body. To be conservative, we anticipate that our resistance and impact-loading regimen will result in a modest increase of ~1%, whereas the active control regimen should have a negligible attenuating effect on BMD loss. Therefore, we anticipate a difference between the exercise and control groups of ~3.5% at the hip, 4.0% at the lumbar spine, and 2.5% for the whole body, which would be clearly clinically significant and substantially reduce the risk for fracture. To achieve 90% power at an alpha level of 0.05 (two-tailed), 40 subjects per group are required to demonstrate a difference between groups at each bone site at the end of the 12-month intervention. Regarding the second main comparison, the resistance training/aerobic group vs. the active control group for change in maximal exercise capacity as measured in metabolic equivalents (METS), 48 subjects per group are required to demonstrate a 0.66 SD difference between groups at the end of the 6-month intervention period and also potentially at 12-month follow-up [38,39]. Previous experience with exercise trials that we have conducted indicates an attrition rate of up to 25% over the course of the study period. However, to be conservative we will account for an attrition rate of up to 35%. Therefore, to adequately ensure that we have sufficient subject numbers at the end of the intervention, 65 subjects will be randomized to each of the three groups (N = 195). A sample size of 195 will also provide us with sufficient power to detect differences in our secondary outcomes.

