Data will be analysed using the SPSS statistical software package. Analyses will include standard descriptive statistics, Student's t tests, correlation and regression, and two-way (group × time) repeated measures ANOVA to examine differences between groups over time. All tests will be two-tailed and an alpha level of 0.05 will be applied as the criterion for statistical significance.

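### The named analyses leave out the stratification factor and use baseline only as a repeated measure, so the comparisons are valid but somewhat less precise than the design allows

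*Protocol article*

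**What the plan says.** Under Subjects, the protocol article states: "Subjects will be stratified according to time on ADT", with the cut at 6 months, ahead of random assignment to the three groups. It gives no reason for choosing this factor and names no other stratifier; in particular, site (Perth or Brisbane) is not one.

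Under Measurements: "Measurements for primary and secondary endpoints will take place at baseline, 6 and 12 months (end of the intervention".

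The last paragraph of Calculation of Sample Size and Statistical Analysis begins "Analyses will include standard descriptive statistics" and goes on to list "Student's t tests, correlation and regression, and two-way (group × time) repeated measures ANOVA to examine differences between groups over time". The ANOVA's two factors are group and time. No stratum term and no baseline covariate is mentioned. Regression is listed without a purpose or any covariates.

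The same section sizes the BMD comparison on change: "standard deviation (SD) for change in our primary outcome of BMD equates to ~4.8%, 3.3%, and 2.5" percent at hip, lumbar spine and total body. When setting the expected losses it remarks that "loss in BMD is greatest in the first year of ADT".

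**The concern.** When randomisation is stratified on a factor that predicts outcome, the arms are balanced on that factor by design. An analysis without the factor still counts its variation as error, so the standard error is larger than the design warrants. The article's remark on first-year bone loss is a reason to expect that time on ADT predicts BMD change.

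Baseline raises a related question. A change comparison subtracts the whole baseline value, whereas ANCOVA subtracts the part that predicts follow-up. In a randomised trial both estimate the same treatment effect, and ANCOVA is at least as precise in large samples.

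What is at stake is the width of the intervals and some power. This matters most for the METS comparison, which has the least room for attrition.

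**Working it through.** **Inputs from the article.** SD of BMD change: 4.8% hip, 3.3% spine, 2.5% total body. Expected differences: 3.5%, 4.0% and 2.5%. METS difference: 0.66 SD. Two-sided alpha 0.05, power 90%, 65 randomised per arm, attrition up to 35%.

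**Inputs assumed, because the article does not give them.** Baseline-to-follow-up correlation ρ from 0.5 to 0.98. Gap D in mean BMD change between the two ADT strata of 1 to 3 percentage points. Strata of equal size. Equal variances at both visits. The 0.66 SD taken on the change scale, as the sentence about change in exercise capacity suggests.

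**Step 1: reproduce the plan's figures.** For an unadjusted two-group comparison of change, n per group = 2(1.960 + 1.282)² × (SD/difference)² = 21.01 × (SD/difference)².

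- Hip: 21.01 × (4.8/3.5)² = 39.5, so 40. This is the stated figure, and the hip is the binding site.
- Spine: 21.01 × (3.3/4.0)² = 14.3, so 15.
- Total body: 21.01 × (2.5/2.5)² = 21.01, so 22.
- METS: 21.01/0.66² = 48.2, so 49 after rounding up. The stated 48 agrees to within one subject.

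The stated sizes therefore correspond to unadjusted comparisons.

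**Step 2: what the named ANOVA does with baseline.** The time factor includes the baseline visit. With baseline and one follow-up visit, the group-by-time interaction is the same test as a t test on change. Baseline is used, but as an outcome level.

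**Step 3: change comparison against ANCOVA.** Variance of ANCOVA relative to change = (1 − ρ²)/[2(1 − ρ)] = (1 + ρ)/2. The standard error of the change comparison is therefore √[2/(1 + ρ)] times that of ANCOVA.

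| ρ | Variance ratio | Change SE wider by | Hip n for 90% power |
|---|---|---|---|
| 0.98 | 0.99 | 0.5% | 40 |
| 0.9 | 0.95 | 3% | 38 |
| 0.7 | 0.85 | 8% | 34 |
| 0.5 | 0.75 | 15% | 30 |

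**Step 4: leaving out the stratum.** With equal strata, the share of variance due to the stratum is (D/2)²/SD², and the unadjusted standard error is too wide by 1/√(1 − share) − 1.

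| D (points) | Hip share | Hip SE wider by | Spine share | Spine SE wider by |
|---|---|---|---|---|
| 1 | 1.1% | 0.5% | 2.3% | 1.2% |
| 2 | 4.3% | 2.2% | 9.2% | 4.9% |
| 3 | 9.8% | 5.3% | 20.7% | 12.3% |

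**Step 5: power at the planned attrition.** 65 × 0.65 = 42.25, so 42 per arm. By the noncentral t, METS power at 0.66 SD is 84.8% without adjustment. With baseline adjustment the standardised difference becomes 0.66/√[(1 + ρ)/2], and power is 86.6% (ρ = 0.9), 90.0% (0.7) or 93.2% (0.5). Unadjusted power for BMD at 42 per arm is about 91% at the hip and above 99% at the spine and total body.

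**Step 6: validity.** In a simulation of 20,000 trials per scenario, with 42 per arm, balanced strata, hip SD 4.8 and D = 2, the type I error of the change comparison without the stratum was 0.046 (ρ = 0.7) and 0.044 (ρ = 0.9), against a nominal 0.05. At ρ = 0.7 the mean standard error was 1.067 for change alone, 1.044 for change with the stratum, and 0.969 for ANCOVA with the stratum.

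**The case against.** The strongest objection is that this is detail a condensed article may omit. The list of analyses is open-ended, it includes regression, which could carry both terms, and a fuller plan may add them. That limits the point, since nothing says the analysis must be unadjusted. It does not remove it: the article attaches group differences over time to a named method with two named factors, neither of which is the stratifier, and gives regression no role in that comparison.

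A second objection is that the benefit is small where it matters most. If ρ for BMD is very high, ANCOVA gains almost nothing. The spine has power to spare, and the hip keeps its 90% target at the planned attrition. All of this stands.

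A third is that the METS gain depends on circumstances. At 25% attrition, the most the team reports from its own trials, 65 × 0.75 = 48.75, so about 48 remain per arm, which is the stated requirement. At 35% attrition, adjustment restores 90% power only if ρ is about 0.7 or lower. This also stands.

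Some stronger readings are tempting but unsupported:

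- **Baseline is ignored.** It is not; the interaction tests change, and the sample size rests on the SD of change. The large loss (standard error 1.4 to 2.3 times that of ANCOVA at ρ of 0.7 to 0.9) would arise only if t tests compared follow-up values alone, which the article does not say.
- **The plan stratifies because bone loss depends on ADT duration.** No reason is given under Subjects. The first-year remark serves the assumed losses, and with a cut at 6 months both strata may contain men in their first year.
- **Omitting site contradicts the design.** Site is not a stated stratifier.

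**Conclusion.** The point holds as one of efficiency. The stratification factor appears in none of the named between-group analyses, and baseline serves as a repeated measure where it could serve as a covariate. No treatment estimate is biased by this and the type I error is not inflated; the test errs slightly on the conservative side if the stratum is prognostic.

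The baseline component ranges from negligible to moderate, depending on ρ. The stratum component is small at the hip and can be larger at the spine, where power is already ample. The practical gain is likely to fall on METS and other outcomes with lower correlation between visits. These sizes rest on values of ρ, stratum gap and stratum split that the article does not supply, so they should be read as ranges. A reader might infer that the BMD comparison is underpowered as planned; the figures do not show that.

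**What to change.** In the final paragraph of Calculation of Sample Size and Statistical Analysis, add a sentence such as: each between-group comparison will be estimated by analysis of covariance, or an equivalent longitudinal model, with the baseline value of the outcome and the ADT-duration stratum used at randomisation as covariates. Site may be added, but this is optional.

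The cost is one or two degrees of freedom (one more if site is included). The outcome baselines and the stratum are already recorded, so no new data are needed, and the sample size need not change. Naming the covariates in advance also removes any later choice about which to include. If a separate analysis plan already specifies these terms, a cross-reference to it is enough.

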### Exercise Intervention

All three exercise groups: (1) resistance/impact-loading exercise; (2) resistance/cardiovascular exercise; and (3) usual care/delayed exercise will train 2 times per week in an exercise clinic. Weight machines will be used to ensure participant safety for those in the resistance/impact-loading exercise and the resistance/cardiovascular exercise groups. The clinic sessions will take approximately 60 minutes (this includes the warm-up and cool-down periods) and will be conducted in the Exercise Clinics at Edith Cowan University in Perth and at The University of Queensland in Brisbane. Sessions will commence with a 10-minute warm-up comprising low-level aerobic activities such as walking and stationary cycling, as well as stretching. The resistance training regimen (groups 1 and 2) will include 6 exercises that target the major upper and lower body muscle groups, which we have used previously in a number of studies [20,26,27,31-33]. The rest period between sets will be 1–2 minutes. To ensure the progressive nature of the training program, subjects will be encouraged to work past the specific repetition maximums (RMs) prescribed. The resistance will be increased by 5–10% increment for the next set/training session if subjects are able to perform more repetitions than the RMs specified during a set. Intensity will be manipulated from 6–12-RM (e.g. the maximal weight that can be lifted 6 to 12 times) using 1–4 sets per exercise.

The impact-loading regimen involves several activities which we have been previously used in a year-long training study in postmenopausal women [34]. For the first 12 weeks, 2 rotations will be performed of skipping (30 sec), bounding over soft hurdles (13–16 cm), and drop jumping (10–15 cm). In the second 12 weeks, hopping on one leg (10 times) will be added, and 3 rotations of all activities will be performed. In the third 12-week period, leaping (10 times) will replace skipping, and for the remainder of the program 4 rotations will be performed of bounding (19–25 cm), drop jumping (20–25 cm), hopping, and leaping. These activities result in substantial peak ground reaction forces ranging from 3.4 to 5.2 times body weight and are deemed to be safe and acceptable by older people and effective for increasing bone accretion [34].

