All exercise sessions will be conducted in small groups of up to 10 participants, with participants exercising in pairs or under direct supervision to ensure correct technique and minimize the risk for injury. Each session will conclude with a 5-minute cool-down period of stretching activities.

In addition to the clinic training, twice weekly home-based training will take place. As with the clinic impact-loading program, the home exercise program will also follow a circuit routine and comprise, in a progressive fashion, 2 to 4 rotations of skipping, hopping, leaping, and drop jumping.

The usual care/delayed exercise group (group 3) will act as a control group for the resistance/cardiovascular group in the initial 6 months and for the resistance/impact loading intervention group for the full 12 months. Participants in this group will be provided with a printed booklet with information about exercise, and in the second 6-month period cycling (non impact) exercise sessions will be undertaken twice a week. Further, we will offer participants in this group a 3-month whole body resistance exercise program following the completion of the second 6-month period.

The resistance/cardiovascular exercise (group 2) will undertake the same resistance training regimen as described above for group (1) that will include 6 exercises that target the major upper and lower body muscle groups for the initial 6 months with a follow up home based program for the remaining 6 months of the program. In addition, each clinic session will include 20–30 minutes of aerobic exercise using various modes such as walking or jogging on a treadmill, cycling or rowing stationary ergometer, or exercising on a cross training machine. Target intensity will be 60%–85% of estimated maximum heart rate (calculated as 220 – age) with individual heart rate monitors (Polar Electra Oy, Finland) provided for each participant. In addition to the clinic training, patients from group 2 will be encouraged to undertake home-based training incorporating aerobic activity (e.g. walking, cycling) with the aim to accumulate at least 150 minutes per week for the duration of the study.

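### Randomisation is stratified by time on ADT but not by site in a two-city supervised-exercise trial; adding site to the scheme and the model is a cheap improvement, not the repair of an error

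*Protocol article*

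**What the plan says.** The abstract (Methods/Design) describes a "Multi-site randomized controlled trial of 195 men (65 subjects per arm) undergoing treatment for prostate cancer involving ADT in the cities of Perth and Brisbane". The Subjects section gives the allocation scheme: "Subjects will be stratified according to time on ADT (< or = 6 months) and randomly assigned to one of the groups listed above". Time on ADT is the only stratification factor named anywhere in the article.

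The Exercise Intervention section says that the clinic sessions "will be conducted in the Exercise Clinics at Edith Cowan University in Perth and at The University of Queensland in Brisbane", and that "All exercise sessions will be conducted in small groups of up to 10 participants", with men working in pairs or directly supervised. Each city therefore has its own clinic.

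For the analysis, the section on sample size and statistical analysis lists descriptive statistics, t tests, correlation and regression, and a two-way repeated-measures ANOVA whose two factors are group and time. Neither site nor the ADT stratum is among those factors.

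**The concern.** The intervention is behavioural, supervised and delivered in groups, so how it is delivered depends on the local clinic. Men come through attending specialists in each area, so the patient mix may differ between cities. Several endpoints (DXA, treadmill gas analysis, applanation tonometry, 1-RM) depend on local equipment or operators. Site is therefore a plausible source of variation in 12-month change, yet nothing in the stated scheme holds the site mix equal across the three arms, and the named ANOVA does not take site variation out of the error term.

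At stake are some precision and the face-value comparability of the arms. The ADT factor has a related problem. Stratifying on a prognostic factor and then leaving it out of the model gives up part of the precision that stratification was meant to buy, because the unadjusted standard error does not reflect the balance achieved.

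**Working it through.** **Inputs.** From the sample size section: 65 men per arm, N = 195; SD of hip BMD change 4.8%, planned hip difference 3.5%; planned METS difference 0.66 SD. Not in the documents, hence assumed: share of men per city (50:50, with splits up to 80:20 as the range), and site difference in change, g = 0.2 to 0.5 SD.

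**1. The plan's own figure.** The plan gives no figure on site. Its sample size supplies the yardstick: "To achieve 90% power at an alpha level of 0.05 (two-tailed), 40 subjects per group are required". For the hip, n = 2(1.960 + 1.282)² / (3.5/4.8)² = 21.02 / 0.532 = 39.5, so 40 per group, as stated. For METS at the same power, 21.02 / 0.66² = 48.3, so 49 against the stated 48 (power at 48 is 89.9%). Both reproduce closely. The planned effects are 3.5/4.8 = 0.73 SD (hip) and 0.66 SD (METS).

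**2. Chance imbalance in site share.** With allocation that ignores site, the SD of the difference in share between two arms is √(2p(1−p)/65). At p = 0.5 this is 0.088, or 8.8 points. A gap of 10 points needs 7 men of 65, and a gap of 15 points needs 10 men. The exact probabilities for two independent binomials (65, 0.5) are 0.254 and 0.095. Simulation (400,000 draws) with all three arms fixed at 65 gives, for one given pair of arms:

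| Larger site's share | SD of difference | P(≥10 points) | P(≥15 points) |
|---|---|---|---|
| 50% | 0.088 | 0.257 | 0.096 |
| 60% | 0.086 | 0.244 | 0.089 |
| 70% | 0.081 | 0.216 | 0.070 |
| 80% | 0.070 | 0.155 | 0.037 |

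**3. Effect on a contrast.** Shift = g × imbalance.
- g = 0.2: 0.2 × 0.10 = 0.02 SD; 0.2 × 0.15 = 0.03 SD.
- g = 0.5: 0.5 × 0.10 = 0.05 SD; 0.5 × 0.15 = 0.075 SD.

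For the hip, 0.02 × 4.8 = 0.10 and 0.075 × 4.8 = 0.36 percentage points, against a planned 3.5. The standard error of a contrast at 65 per arm is √(2/65) = 0.175 SD, so the largest of these shifts is 0.075/0.175 = 0.43 of one standard error. It is also 0.075/0.73 = 10% of the planned hip effect and 0.075/0.66 = 11% of the planned METS effect.

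**4. Variance explained by site.** At 50:50 this is p(1−p)g²: 0.25 × 0.04 = 1% for g = 0.2, and 0.25 × 0.25 = 6% for g = 0.5. Removing 6% of the variance is worth about 65 × 0.06 ≈ 4 men per arm. Removing 1% is worth less than one.

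**5. Feasibility.** Two sites by two ADT categories gives four strata: 195/4 ≈ 49 men each on average, or about 16 per arm per stratum.

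**The case against.** A reader might infer that an unequal site mix confounds the arm comparison, or that the planned tests are invalid without a site term. The documents do not support either reading. Randomisation that ignores site is unbiased in expectation, and the chance imbalance it leaves is part of the sampling error that the unadjusted tests already count, so the type I error holds. A stable difference in level between sites, such as a fixed scanner offset, cancels when change or group-by-time is analysed. Only a site difference in change matters, and 0.5 SD is an upper-end assumption with no figure behind it, not far below the 0.66 SD effect the trial is powered to detect. These points stand.

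A reader might also count the chance that any of the three pairs of arms is unbalanced by 10 points or more (33 to 49% over the splits above). That overstates the issue, because it includes the pair of exercise arms, and the powered comparisons are each exercise arm against control. Nor can an argument from clinic session capacity be sized: the article gives a group size but no capacity.

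Time on ADT is itself a reasonable choice of factor, since the sample size section says bone loss is greatest in the first year of ADT. The article is also brief. Separate lists per clinic are neither stated nor excluded, regression is among the listed methods and could carry site, and covariates are commonly left to an analysis plan that is not shown. The missing site term is therefore no finding on its own. What remains is that the article does state a stratification scheme and does name a two-factor ANOVA, and a standard, inexpensive scheme would serve this two-centre trial better.

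**Conclusion.** The point holds as a cheap improvement, not as an error in the plan. As written, site balance is left to chance: about a 25% probability of a gap of 10 points or more between two given arms and about 10% for 15 points or more at a 50:50 split, falling to about 15% and 4% at 80:20. The gain from fixing it is balance and modest precision, not the removal of bias. The size depends on two assumptions that the documents do not settle: the split between cities, and a site difference in change of 0.2 to 0.5 SD. The point about the scheme falls away if the full protocol already randomises from separate lists per site.

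**What to change.** In Subjects, stratify the randomisation by site (Perth, Brisbane) as well as time on ADT, giving four strata, unless the full protocol already uses separate lists per site. In the statistical analysis paragraph, include site and time-on-ADT stratum as factors in the between-group model, so that the analysis matches the randomisation.

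If randomisation has already begun, leave the list alone and make the model change only. That recovers the precision but does not balance the arms by site.

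Cost: a change to the randomisation list, four strata instead of two, and two extra model terms. With about 16 men per arm in an average stratum this is workable, even if recruitment is uneven between the cities.
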